# Study protocol: the effect of whole body vibration on acute unilateral unstable lateral ankle sprain- a biphasic randomized controlled trial

**DOI:** 10.1186/1471-2474-14-22

**Published:** 2013-01-14

**Keywords:** Whole body vibration, Ankle sprain, Rehabilitation, Functional treatment

## Abstract

**Background:**

Ankle sprains often result in ankle instability, which is most likely caused by damage to passive structures and neuromuscular impairment. Whole body vibration (WBV) is a neuromuscular training method improving those impaired neurologic parameters. The aim of this study is to compare the current gold standard functional treatment to functional treatment plus WBV in patients with acute unilateral unstable inversion ankle sprains.

**Methods/Design:**

60 patients, aged 18–40 years, presenting with an isolated, unilateral, acute unstable inversion ankle sprain will be included in this bicentric, biphasic, randomized controlled trial. Samples will be randomized by envelope drawing. All patients will be allowed early mobilization and pain-dependent weight bearing, limited functional immobilization by orthosis, PRICE, NSARDs as well as home and supervised physiotherapy. Supervised physical therapy will take place twice a week, for 30 minutes for a period of 6 weeks, following a standardized intervention protocol. During supervised physical therapy, the intervention group will perform exercises similar to those of the control group, on a side-alternating sinusoidal vibration platform. Two time-dependent primary outcome parameters will be assessed: short-term outcome after six weeks will be postural control quantified by the sway index; mid-term outcome after one year will be assessed by subjective instability, defined by the presence of giving-way attacks. Secondary outcome parameters include: return to pre-injury level of activities, residual pain, recurrence, objective instability, energy/coordination, Foot and Ankle Disability Index and EQ 5D.

**Discussion:**

This is the first trial investigating the effects of WBV in patients with acute soft tissue injury. Inversion ankle sprains often result in ankle instability, which is most likely due to damage of neurological structures. Due to its unique, frequency dependent, influence on various neuromuscular parameters, WBV is a promising treatment method for patients with acute unstable inversion ankle sprains.

**Trial registration:**

NCT01702597

## Background

Lateral ankle sprains are one of the most common musculoskeletal injuries
[1,2]. They mostly result from an internal rotation and adduction of the plantarflexed foot with subsequent damage to the lateral capsulo-ligamentous complex. About 65% of all lateral ankle sprains are isolated anterior tibio-fibular ligament (ATFL) injuries, while 20% are combined ATFL and calcano-fibular ligament injuries
[3]. 85% of all ankle injuries are ankle sprains and 85% of those are inversion sprains
[4], with about one ankle sprain occurring per 10.000 people every day
[5]. Although usually considered an innocuous injury, three-year full recovery rates range from 36% to 85%
[6].

Ankle instability is most likely caused by damage to passive structures and neuromuscular impairment
[7]. Damage to passive structures, i.e. capsular structure and ligaments, results in objective (anterior drawer, talar tilt) and subjective instability (giving-way)
[3]. Neurological impairments include muscle fatigue
[7-9], reduced dynamic balance
[10-12] and impaired postural control
[13-15]. Although not all patients with functional (FAI) or chronic ankle instability (CAI) present with objective instability, they are all thought to have neuromuscular impairments
[2,16,17]. This results in lower physical activity levels
[18], diminished quality of life
[19], and a possible increase in the risk of osteoarthritis
[20,21].

Any treatment plan should therefore address both damaged passive structures and neuromuscular impairment. Generally, three treatment regimens are available: functional treatment (early mobilization and bracing), cast immobilization for 2–6 weeks, or operative treatment
[22,23]. A Cochrane review from 2007 comparing conservative and surgical treatments found similar outcomes
[3]. Therefore, functional treatment has to be considered the current gold standard. Functional treatment should allow healing of damaged passive structures and compensate for neuromuscular impairments, i.e. improve muscle strength and proprioception. Physical therapy therefore includes stretching, body-weight exercises, training apparatus and devices (for example wobble board training). Supervised rehabilitation has proven superior to conventional treatment
[24,25].

A neuromuscular training method gaining increased attention is whole body vibration (WBV). WBV involves synchronous or side-alternating sinusoidal vibrations, which are transmitted to the body via platforms. It is believed to evoke muscle contractions via stretch reflexes in the muscle spindle system
[26-28]. A growing body of evidence indicates improvements of various neuromuscular parameters following WBV, such as power, strength, movement velocity, range of motion and balance
[29-38]. Reports to the contrary
[39,40] may be due to heterogeneous patient populations and varying intervention protocols, which in turn can be due to limited knowledge of the dose-effect relationship, i.e. vibration frequency and amplitude.

In general, frequencies <10Hz are believed to loosen muscle and tissue. Frequencies >10Hz and <20Hz still allow active contraction and relaxation of muscle fibers and are used for coordination exercises. Frequencies >20Hz result in isotonic muscle contraction
[41]. Vibration amplitude seems to be positively correlated to muscle activity
[42-44]. Although WBV has numerous contraindications, as listed in Table 
1, the only adverse side effects reported are temporary hyposensitivity of the foot soles
[45].

**Table 1 T1:** Inclusion- and exclusion criteria

**Inclusion criteria**	**Exclusion criteria**
Age: 18 to 40 years	Pregnancy
Acute, unilateral, unstable, inversion ankle sprain (Grade II, III)	Conditions affecting the neuromuscular or musculoskeletal system
Signed informed consent	Previous surgical interventions to the foot, ankle, knee or hip; known FAI, CAI
Patient can read and understand German	Conditions possibly affecting balance
	Cardiovascular disease including thrombosis
	Respiratory diseases
	Abdominal diseases (including gallstones)
	Urological diseases (including kidney and bladder stones)
	Gynaecological diseases and + intrauterine devices
	Neurological diseases including epilepsy within the last 2 years
	Acute injuries to the head
	Patient is not available for follow-up visits
	Patient unable to give informed consent
	Patient suspected to be non-compliant

Functional classification system for lateral ankle sprains: Grade II: hematoma/swelling/pain on palpation and positive anterior drawer test (complete tear of the ATFL, incomplete tear of the CFL); Grade III: hematoma/swelling/pain on palpation and positive anterior drawer test and positive talar tilt test (complete tear of the ATFL and CFL); adapted from
[46-48]; FAI: Functional ankle instability; CAI: Chronic ankle instability.

With WBV improving range of motion (ROM), power and balance - parameters known to be affected in patients with ankle instability - it might be beneficial to include it into the current functional treatment regime. To our knowledge only one study investigated the effects of WBV in patients with ankle instability. Cloak at al.
[49] conducted a randomized controlled trial (RCT) on functional ankle instability in dancers (n=38), comparing WBV to a control group (regular dance training). The WBV group yielded significantly better results for balance (STAR extrusion balance test) as well as a significantly reduced Center of Pressure values.

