**Secondary Outcome parameters**	
Return to pre-injury level of activity (work, sports)	[dichotomous variable]
Residual pain:	
Pain at rest	[dichotomous variable; VAS]
Pain on weight-bearing	[dichotomous variable; VAS]
Pain during sports	[dichotomous variable; VAS]
Subjective Instability (Giving-way)	[dichotomous variable]
Recurrence	[dichotomous variable]
Objective instability:	
Anterior drawer	[dichotomous variable]
Talar tilt	[dichotomous variable]
Ankle ROM	[numeric, scale]
Postural control: Balance Test (Sway index)*	[numeric, scale]
Energy/coordination:	
Multiple one leg hopping*	[numeric, scale]
Single two leg jump*	[numeric, scale]
Complications	[text]
Scores:	
Foot and Ankle Disability Index [60]	[numeric, scale]
EQ 5D 5L	[numeric, scale]

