### Adverse events

The only adverse side effects of WBV reported in literature were temporary hyposensitivity of the foot soles
[45]. Possible adverse events related to the interventions include pain, fall from the WBV device/wobble board, and delayed mobilization or healing. Unexpected events related to data acquisition might be patients’ inability to perform certain load-dependent examinations. Severe adverse events are only expected following a fall from the training device.

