## Discussion

The present study protocol on the effect of WBV in patients with acute, unilateral, unstable inversion ankle sprains is the first study to apply WBV in patients with acute soft tissue injuries. Due to its influence on various neuromuscular parameters, which are known to be impaired in patients with ankle instability, WBV provides a novel, functional treatment approach for this problem.

Several limitations of the present protocol must be discussed. First of all, the authors have decided to use a functional classification system. With ankle instability being the most important parameter for further treatment decision, an established functional classification system was chosen. Ankles are classified into stable or unstable based on clinical presentation and examination (swelling, anterior drawer test and talar tilt test)
[46-48]. In case initial examination is not tolerated, delayed physical examination has been shown to be equal to arthrography (specificity/sensitivity: 85%/96%)
[63-65]. Its feasibility in daily practice and high sensitivity makes it a suitable classification system for patients with acute inversion ankle sprains.

Second, as discussed in the introduction, functional treatment seems to be the current gold standard treatment approach. Still, immobilization, as well as type and duration of physiotherapy are a matter of discussion. Kerkhoffs et al.
[66] conducted a systematic review on the effectiveness of various braces/bracing methods for acute ankle sprains and found lace-up supports to be the most effective, which seems supported by a Cochrane Review
[3]. A recent single-blinded RCT by Lamb et al.
[67] found a short period of immobilization in an Aircast brace to result in faster recovery than double-layered tubular compression bandage. This is in line with a review by Kemle et al.
[23] who found evidence pointing towards the superiority of ankle braces. Consequently, initial immobilization will be realized with an ankle brace. Moreover, the type and duration of functional rehabilitation remains unclear. Our supervised rehabilitation protocol is based on the guidelines of the Royal Dutch Society of Physical Therapy
[52], which is comparable to other published treatment protocols
[53-57,68]. Although the optimal intensity of physical rehabilitation remains unclear, 45 minutes, twice to three times a week over a period of 6–8 weeks seem to be beneficial

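### Anterior drawer and talar tilt define entry and grade, yet are scored only yes/no as outcomes: drawer cannot record worsening in anyone, tilt cannot in Grade III, and a pooled tilt proportion mixes two questions (minor)

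*Protocol article*

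**What the plan says.** - **Who enters.** The inclusion criterion in Table 1 is "Acute, unilateral, unstable, inversion ankle sprain (Grade II, III").
- **How grade is defined (Table 1 footnote).** "Grade II: hematoma/swelling/pain on palpation and positive anterior drawer test (complete tear of the ATFL, incomplete tear of the CFL") and "Grade III: hematoma/swelling/pain on palpation and positive anterior drawer test and positive talar tilt test (complete tear of the ATFL and CFL"). A positive anterior drawer is required for both grades. A positive talar tilt is listed for Grade III only, so a Grade II ankle is negative on it by implication.
- **How the classification is made (Discussion).** "Ankles are classified into stable or unstable based on clinical presentation and examination (swelling, anterior drawer test and talar tilt test").
- **What is measured as outcome.** Table 3, under Secondary Outcome parameters, has the entry "Objective instability" with two lines, anterior drawer and talar tilt, each typed as a dichotomous variable. The Abstract confirms the secondary status: "Secondary outcome parameters include: return to pre-injury level of activities, residual pain, recurrence, objective instability".
- **Allocation and analysis.** The section on study centers, population, screening and randomization describes envelope drawing and mentions no stratification by grade. The statistics section names descriptive statistics, Student's t-test and Fisher's exact test. Neither test takes entry status into account.
- **Possible harms (Adverse events).** "Possible adverse events related to the interventions include pain, fall from the WBV device/wobble board, and delayed mobilization or healing".

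**The concern.** The same two examinations decide whether a patient is eligible, which grade the patient has, and whether the ankle counts as objectively unstable later. Two problems follow.

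1. **No room above the entry value.** A sign that is positive at entry can only stay positive or clear. An ankle that becomes looser than it was at entry looks the same as one that is unchanged. The Background treats these two tests as the objective signs of damage to passive structures. The article also describes the trial as the first use of vibration in acute soft tissue injury and names delayed healing as a possible harm. These are therefore the outcomes in which a reader would look for ligament harm.
2. **One proportion, two questions.** At follow-up, a positive talar tilt in a Grade III patient means that laxity persisted. In a Grade II patient it means that laxity is new. A single pooled proportion per arm does not separate these, and it shifts with the number of Grade III patients each arm happens to receive.

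**Working it through.** **No figure to reproduce.** The article gives no calculation for these outcomes. The total of 60 was chosen by reference to previous studies.

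**Step 1: entry status against the outcome scale** (Table 1 footnote against Table 3)

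| Test | Grade | At entry | What yes/no scoring can record |
|---|---|---|---|
| Anterior drawer | II | positive | persistence or resolution |
| Anterior drawer | III | positive | persistence or resolution |
| Talar tilt | II | negative (implied) | stays negative or becomes positive |
| Talar tilt | III | positive | persistence or resolution |

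The drawer test can record worsening in 0 of 60 patients. Talar tilt can record it in every Grade II patient and in no Grade III patient.

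**Step 2: the Grade III share (assumption).** The article does not state it. The Background gives 65% isolated ATFL injuries, "while 20% are combined ATFL and calcano-fibular ligament injuries". Treating the combined injuries as Grade III gives 20/(65 + 20) = 24%, or 14 of 60. This mapping is loose. Table 1 puts incomplete CFL tears in Grade II, and the Background shares refer to all lateral sprains, not only unstable ones. I therefore use a range of 24% to 50%, that is K = 14 to K = 30 Grade III patients. Grade II patients then number 46 down to 30.

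**Step 3: chance imbalance in grade.** I assume 30 per arm, since the article gives no ratio. The number of Grade III patients X in one arm is hypergeometric (60 patients, K of Grade III, 30 drawn), and the gap between arms is |2X − K|.

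| K | P(gap ≥ 4 patients) | P(gap ≥ 6 patients) | SD of the difference in Grade III share |
|---|---|---|---|
| 14 (24%) | 0.36 | 0.125 | 11 points |
| 30 (50%) | 0.44 | 0.196 | 13 points |

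The gap has the same parity as K. For an odd K, a gap of 4 or more means 5 or more, and the probability over this range is 0.23 to 0.30. The SD is not affected by parity.

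**Step 4: how much of this reaches the follow-up result.** If a fraction q3 of Grade III and q2 of Grade II ankles are tilt-positive at follow-up, the SD carried into the arm difference is SD(grade share) × (q3 − q2). The rates are assumed:
- q3 = 0.30, q2 = 0.05: 11 × 0.25 = 2.8 points at K = 14; 13 × 0.25 = 3.3 points at K = 30.
- q3 = 0.50, q2 = 0.05: 11 × 0.45 = 5.0 points at K = 14; 13 × 0.45 = 5.9 points at K = 30.
- Full carry-over of 11 to 13 points needs q3 = 1 and q2 = 0, meaning no healing in Grade III and no new laxity in Grade II.

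**Step 5: bias and type I error.** I simulated 20,000 trials per scenario with no treatment effect, for shares of 24%, 35% and 50% and q3/q2 of 1/0, 0.5/0.05 and 0.3/0.05. The mean arm difference was within 0.2 percentage points of zero throughout. Fisher's exact test at two-sided 0.05 rejected in 1.1% to 2.8% of trials.

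**Step 6: what stratifying by grade gains.** With Grade III share p and overall rate m = p·q3 + (1 − p)·q2, the part of the outcome variance due to grade is p(1 − p)(q3 − q2)² / [m(1 − m)].
- p = 0.233, q3 = 0.5, q2 = 0.05: m = 0.155; 0.0362/0.131 = 28%.
- p = 0.5, q3 = 0.3, q2 = 0.05: m = 0.175; 0.0156/0.144 = 11%.

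**Step 7: can the drawer test still show slower healing?** The power for persistence rates p1 and p2 is Φ{[|p1 − p2| − 1.96·√(2p̄(1 − p̄)/30)] / √[(p1(1 − p1) + p2(1 − p2))/30]}, where p̄ is the mean of the two.
- 0.40 vs 0.10: (0.300 − 0.219)/0.105 = 0.77, power 78%.
- 0.50 vs 0.20: power 69%.
- 0.30 vs 0.10: power 49%.

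Fisher's exact test is conservative, so its power would be somewhat lower. These rates are also assumed.

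**The case against.** The strongest reply is that a sign present in everyone at entry is an ordinary basis for a resolution outcome. The short-term and mid-term hypotheses both ask about improvement. If vibration delays healing, more ankles stay drawer-positive in that arm, and the yes/no outcome can show it (step 7). This stands. What is lost is only the ankle that becomes looser than it was at entry.

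Two stronger readings are tempting and are not supported.
- A reader might infer that neither test can show worsening. This is wrong for talar tilt in Grade II, where a negative ankle can turn positive. Under the assumed range that covers 30 to 46 of the 60 patients.
- A reader might infer that the talar-tilt comparison simply follows the grade mix and is biased by it. This is true of the entry value only. Follow-up status also depends on healing, allocation is random, and steps 4 and 5 show a partial carry-over with no bias and no excess of false positives.

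It is also fair to say that a fuller protocol or an analysis plan may add graded laxity or an entry-adjusted analysis, and that the statistics section does not claim to be exhaustive. The yes/no scale is nonetheless stated in Table 3, and the overlap with the entry criteria follows from the article's own definitions. The point therefore does not rest on silence.

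**Conclusion.** The concern holds in a limited form and is minor. By the article's own definitions, the drawer outcome has no room for worsening in any patient, and the talar-tilt outcome has none in Grade III. Talar tilt pooled over grades combines persistence with new laxity. The cost is some precision and a blurred reading: an SD of about 3 to 6 points added to the arm difference under the assumed healing rates, and 11 to 13 points only in the extreme case.

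The definitional part needs no assumption beyond reading Grade II as tilt-negative. The sizes rest on 30 per arm, a Grade III share of 24% to 50%, and assumed follow-up rates, none of which the article gives. No primary outcome, hypothesis or stated number is affected.

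**What to change.** 1. State the anterior drawer outcome as resolution versus persistence of a sign present at entry.
2. Compare talar tilt between arms stratified by entry grade, for example with an exact stratified or Mantel-Haenszel test. Show persistence in Grade III and new positives in Grade II separately, as descriptive results.
3. Optionally, also record an ordered laxity grade against the uninjured ankle at entry and at each follow-up, so that increased laxity becomes visible. Injury is unilateral by inclusion, so a comparison side exists.

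Items 1 and 2 are changes of wording and analysis that use the entry grade the trial already determines. They need no extra patients or visits. Under the assumed rates, item 2 removes about 11% to 28% of the talar-tilt outcome variance. Item 3 needs a line on the case report form and a manual examination of the other ankle.

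The downsides are small strata (perhaps 14 patients in Grade III, so those results stay descriptive) and manual grading that may be less reproducible than a yes/no call. For that reason the ordered grade should supplement the yes/no score, not replace it.

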### Aim of study

The aim of this bicentric, biphasic, randomized, controlled study is to compare current gold standard functional treatment to functional treatment plus WBV in patients with acute unilateral unstable inversion ankle sprains over a period of 12 months.

### Hypotheses

1. Short term results (after 6 weeks): H_0_ = Functional treatment in combination with WBV therapy in patients with acute unilateral unstable inversion ankle sprains does not improve the Sway-Index compared to functional treatment alone.

2. Mid-term results (after 12 months): H_0_ = Functional treatment in combination with WBV therapy in patients with acute unilateral unstable inversion ankle sprains does not result in a reduction of the recurrence rate compared to functional treatment alone.

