## Methods/Design

### Study design and protocol

The study design is a bicentric, biphasic, randomized, controlled trial, following the CONSORT statement guidelines
[50]. 60 patients will be randomized into an intervention (supervised functional treatment and WBV) or control group (supervised functional treatment). Intervention will take place twice a week at a rate of 30 minutes per session, for 6 weeks. Figure 
1 schematically illustrates the study protocol.

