**Primary Outcome parameter (2)**	
(mid-term; 1 year)	
Subjective Instability (Giving-way)	[dichotomous variable]
	

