### Sample size estimation and statistics

With this study being the first using WBV with acutely injured patients, data to conduct sample size estimation is lacking. Therefore sample size was chosen according to previous studies on WBV or ankle instability
[32,49,61,62].

Statistical methods used will include descriptive statistics, Student’s *t*-test and Fisher’s exact test.

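### The 12-month hypothesis is stated on recurrence, but the declared 12-month primary outcome is giving-way, and recurrence is listed separately as secondary

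*Protocol article*

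**What the plan says.** **Hypotheses, item 2 (12 months).** The null hypothesis is that vibration plus functional treatment "does not result in a reduction of the recurrence rate compared to functional treatment alone".

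**Abstract, Methods/Design.** The second primary outcome is given as "mid-term outcome after one year will be assessed by subjective instability, defined by the presence of giving-way attacks". The same paragraph puts recurrence in the other list: "Secondary outcome parameters include: return to pre-injury level of activities, residual pain, recurrence, objective instability".

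**Table 3.** Primary Outcome parameter (2), mid-term at 1 year, is "Subjective Instability (Giving-way"), a dichotomous variable. Under the secondary outcomes, giving-way appears again, and the next line is a separate item: "Recurrence [dichotomous variable"].

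**Hypotheses, item 1 (6 weeks), for comparison.** The null hypothesis is that the combination "does not improve the Sway-Index compared to functional treatment alone". This matches Primary Outcome parameter (1) in Table 3.

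**The concern.** A null hypothesis and the primary outcome meant to test it should name the same variable. At 12 months they do not. The hypothesis is about recurrence, which the outcome list ranks as secondary. The outcome ranked as primary, giving-way, has no hypothesis.

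This affects what the trial may claim at one year. If giving-way differs between groups and recurrence does not, the declared primary outcome is positive but the stated null hypothesis is not rejected. If recurrence differs and giving-way does not, the null hypothesis is rejected by a variable that is not the declared primary outcome. In both cases a report could cite some part of the published protocol in support of calling the result the planned 12-month finding.

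**Working it through.** The point is settled by comparing the text. The arithmetic below only tests whether an error rate can be attached to it.

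**Step 1. Line up hypotheses and outcomes.**

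| Time | Variable in the hypothesis | Primary outcome (abstract and Table 3) | Agree? |
|---|---|---|---|
| 6 weeks | Sway Index | Sway Index | yes |
| 12 months | recurrence rate | giving-way (subjective instability) | no |

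**Step 2. Are recurrence and giving-way one variable under two names?** Table 3 gives them separate lines, each dichotomous. The abstract names giving-way as primary and recurrence as secondary in consecutive sentences. The article nowhere equates them. The plan therefore treats them as two variables.

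**Step 3. Does another section resolve it?** The section on sample size and statistics names the t-test and Fisher's exact test but assigns neither to an outcome or a hypothesis. The sample size does not point to one variable either: "Therefore sample size was chosen according to previous studies on WBV or ankle instability". There is no calculation to reproduce.

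**Step 4. Can a false-positive rate be stated?** The article gives a total of 60 ("60 patients will be randomized into an intervention (supervised functional treatment and WBV) or control group (supervised functional treatment") but no allocation ratio, significance level or event rate. Assumptions: 30 per arm, a two-sided 5% level, Fisher's exact test on each endpoint, and the same true event rate in both arms.

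- Textbook figure for two independent tests, each of true size 5%: 1 − 0.95² = 9.75%.
- Actual size of Fisher's test: s = the sum of P(i)·P(j) over all tables with p ≤ 0.05, where i and j are binomial counts out of 30.
- Two independent endpoints with the same event rate: 1 − (1 − s)².

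| Assumed event rate | Size s, one endpoint | Two independent endpoints |
|---|---|---|
| 10% | 0.9% | 1.9% |
| 20% | 2.2% | 4.4% |
| 30% | 2.6% | 5.2% |
| 40% | 2.6% | 5.1% |
| 50% | 2.7% | 5.4% |

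Counting only results that favour vibration halves s, and the right-hand column becomes 0.9% to 2.7%. Positive correlation between the endpoints would lower it further. The answer depends on inputs that the article does not give, and 9.75% does not describe this test at this sample size.

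**Step 5. Does the choice of variable matter for the analysis?** It does if the two event rates differ. As an illustration only, with assumed rates and 30 per arm, the power of Fisher's test to detect a halving is 10% for 20% against 10%, and 41% for 50% against 25%. The article gives no rate for either variable, so this shows dependence and not the trial's actual power.

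**The case against.** The strongest reply is that the outcome hierarchy is clear. Giving-way is primary and recurrence secondary in both the abstract and Table 3. The Hypotheses section does not use the word primary, so one word in one sentence may be a slip. A team that promoted recurrence would contradict two parts of its own protocol.

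Much of this stands. The two endpoints are not freely interchangeable, and a reader who infers an open choice between them goes further than the text allows. Calling item 2 the primary hypothesis is an inference, though a sound one: there are two hypotheses and two primary outcomes, they share the same time labels, and the first pair matches exactly. If item 2 were not the primary hypothesis, the 12-month primary outcome would have no hypothesis at all, which is no better.

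It might also be said that recurrence was loose wording for recurrent giving-way. The separate lines in Table 3 count against that. Nor is this a detail that an article leaves to a fuller document: the article makes two statements that do not fit together, and a later analysis plan could only override one of them.

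Three stronger readings are tempting and unsupported:

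- **A false-positive risk of 9.75%.** This needs a true size of 5% per test and independence. Neither is established, and Fisher's test at about 30 per arm falls well short of 5%.
- **Recurrence as a new sprain and giving-way as a mere feeling.** The article does not define recurrence, and it defines subjective instability by the presence of attacks.
- **A confirmatory test already assigned to a secondary variable.** The statistics section assigns no test to any endpoint.

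**Conclusion.** The point holds as an internal inconsistency in the current text. Hypothesis 2 and the declared 12-month primary outcome name different variables, so the declared outcome does not test the stated null hypothesis. One of the trial's two primary questions is affected; the 6-week question is not.

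The conclusion rests on the wording alone, and on reading the two hypotheses as belonging to the two primary outcomes with the same time labels. It does not depend on how recurrence is defined or on any error rate, and no reliable error-rate figure can be given. It should be corrected because it determines what the trial can conclude at one year.

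**What to change.** Before any 12-month outcome data are seen, make the hypothesis and the primary outcome name the same variable. There are two ways to do this:

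1. **Simplest, and in line with the abstract and Table 3.** Reword Hypothesis 2 so that the null hypothesis is that the combined treatment does not reduce the proportion of patients with giving-way attacks at 12 months. Keep recurrence as secondary.
2. **If recurrence was intended.** Define it, and make it the 12-month primary outcome in the abstract and Table 3.

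The first option costs one sentence. The second costs a definition and two edits. Neither changes patient numbers, visits or procedures. Consistency does not require a separate hypothesis for the variable that stays secondary. The registry entry was not available here, so no discrepancy with it is alleged.
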